### Objectives

In this study, the aim is to evaluate whether using a commercially available AI tool certified for paediatric use could help HCPs make better decisions about patient care.

Primary objective:

Determine differences in diagnostic accuracy rates of HCPs for paediatric fracture detection, before and after using the AI tool.

Secondary objectives:

Determine whether differences in accuracy rates or effect of adding AI varies according to job role and experience.Determine whether user confidence in fracture diagnosis changes when using the AI tool.Determine whether management plans are altered following the use of the AI tool.

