## Methods and analysis

### Study design

The overall study design is of a cross-over multireader multicase (MRMC) study, where each reader (a HCP) will act as their own control across two imaging interpretation stages, with an interval washout period of at least 4 weeks duration (figure 1). Differences in diagnostic accuracy rates between stages, changes in reader’s confidence rates and simulated patient management will be compared. Subgroup analyses will be conducted according to reader specialty area, experience and body part interpreted.

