**Figure 1 F1:**
[figure not shown]
A diagrammatic flow chart of the multireader multicase (MRMC) study outline. AI, artificial intelligence.

At the first interpretation stage (1 September 2024–31 October 2024), each reader will review a dataset of 500 paediatric limb radiographs (some normal and some abnormal) without AI assistance, then after the washout period (1 November 2024–30 November 2024), they will proceed with the second interpretation stage (1 December 2024–31 January 2025) where they will each read the same dataset with AI assistance. The order of the radiographs, and thus imaged body parts and those with and without abnormalities, will be randomly ordered within the dataset for every reader at each interpretation stage to further reduce recall bias.

Readers will complete the imaging interpretations online, via a password-protected and secure imaging platform (details below). They will be given a 2-month period to complete the exercise and are informed not to seek help in the imaging interpretation with anyone else. Clinical information associated with each radiograph will include the age of patient and gender. Mechanism of injury, pain location, history will not be provided. The reader will be asked to assume that there is generalised pain at the joint in question, and no significant medical history (ie, no genetic or metabolic bone disorder or known malignancy).

Feedback requested from each reader for each radiograph will include:

Marking the site of a fracture on each image (or selecting ‘no fracture’).Confidence in their decision using a 5-point Likert scale (1=not confident; 5=absolutely certain).Selecting the most likely management for the patient. This will be done by providing each reader with a drop-down menu of seven predefined plans, tailored to each subspecialty, with the option for free-text comment. Examples of the different options are provided in figure 2.

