We anticipate a minimum of 40 readers (approximately 14 readers from each specialty) equally split between trainees and consultant-level experience. Each reader will be provided instructions on how to participate in the study and complete a consent form online asking about their demographic details, job role/specialty and experience level. Prior to any interpretation, a short video and instruction sheet on how to use the online reporting platform will be provided. Reporters will be asked to replicate their usual reporting practices as far as possible (eg, use of a suitable monitor, dim lighting) and would be able to use reference tools (eg, textbooks or websites) that they would normally consult for this task, but just not to consult other reporters.

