### Statistical methods/data analysis plan

The STARD-AI (Standards for Reporting of Diagnostic Accuracy - Artificial Intelligence) and CLAIM (Checklist for AI in Medical Imaging) guidelines will be adhered to in the reporting of this study.^33 34^ Diagnostic accuracy of the readers (with and without AI assistance) for each body part will be derived (ie, sensitivity, specificity, positive predictive value and negative predictive value). A true positive result will be counted if a mark made by a reader at the site of a suspected fracture falls within the area of the predefined ‘ground truth bounding box’ area set by the reference radiologists. If the mark made by a reader falls outside a bounding box, it will be counted as a false positive. Where a bounding box was set by the ground truth, but no mark made on the image then a false negative result will be assigned to the reader.

Estimates of these accuracy statistics will be derived through multilevel logistic regression models, with the reader included as a random-intercept. From these models, we will report 95% CIs, and p values (significance level set at 5%). Independent variables will be added, including the reader’s job role and experience, to assess their relationship with diagnostic accuracy. We will additionally present these same statistics to the reader, as derived through the random effects of the models, to explore the relationship between sensitivity and specificity. Intraobserver variability for the diagnostic accuracy of fracture detection before and after the use of AI assistance will also be evaluated, with subanalysis conducted to account for different reader medical specialty subgroups.

We will assess for differences in confidence scores for correctly identified images between HCPs with and without AI guidance, and also whether there were significant differences between readers across specialties and experience levels. We will also evaluate how an indeterminate AI reading affects reader decisions.

Changes in clinical management will be compared using descriptive statistics (ie, frequency and percentages) to determine, for example, how many children would be discharged with a missed fracture, or unnecessary second opinions/additional imaging sought for cases with and without AI assistance. This could provide information to help estimate potential future benefit and cost savings to the NHS at a future clinical implementation stage, where appropriate.

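### The confidence comparison is limited to correctly identified images, which is narrower than the confidence objective and selects on an outcome that AI may change

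*Protocol article*

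**What the plan says.** The secondary objective in the protocol article (Objectives) carries no restriction on which readings count: "Determine whether user confidence in fracture diagnosis changes when using the AI tool". Nor does the design statement (Study design): "changes in reader’s confidence rates and simulated patient management will be compared".

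Data collection matches that breadth. In the list below Figure 1, the article states: "Feedback requested from each reader for each radiograph will include". Confidence on a scale of 1 to 5 is one of the listed items, so scores will exist for right and wrong readings alike. In the second stage readers return to the same images: "they will each read the same dataset with AI assistance".

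The analysis section (Statistical methods/data analysis plan) is narrower: "We will assess for differences in confidence scores for correctly identified images between HCPs with and without AI guidance". The rest of that sentence adds comparisons across specialties and experience levels but names no other set of images. The next sentence concerns how an indeterminate AI output affects decisions, and the management analysis is descriptive. Neither addresses confidence when the reading is wrong.

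Correctness itself is the subject of the primary objective: "Determine differences in diagnostic accuracy rates of HCPs for paediatric fracture detection, before and after using the AI tool".

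**The concern.** Two things are at stake.

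First, the analysis selects readings on something AI may alter. A reading that is wrong without AI and right with it enters only the aided set. A reading that AI turns wrong leaves it. If those readings tend to carry lower confidence, mean confidence among correct readings moves even when no reader's confidence in any image has changed. Such readings are likely here, because the inclusion criteria deliberately remove obvious fractures.

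Second, wrong readings drop out. The Introduction says the study should show how the tool may help or hinder staff. A reader who becomes surer of a wrong answer after a misleading AI output is one form of hindrance, and the stated comparison cannot detect it.

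**Working it through.** The article gives no figure for the confidence comparison, so there is nothing to reproduce. Its sample size concerns the area under the ROC curve and has no bearing on this point.

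**Inputs from the article:** at least 40 readers; 500 images per reader per stage; the same images in both stages; a 1 to 5 confidence scale. **Assumed inputs:** all accuracies and confidence levels below.

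**1. Correctness judged separately in each stage, true AI effect on confidence set to zero.** Let a0 and a1 be accuracy without and with AI, s the share of readings that go from right to wrong, and k = a0 - s the share right in both stages. The share that goes from wrong to right is g = a1 - k. Confidence is e for readings right in both stages and h for readings right in one stage only, and is the same in both stages for any given reading.

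- Mean confidence among correct readings without AI: (k·e + s·h)/a0
- With AI: (k·e + g·h)/a1
- Difference: -(e - h)(a1 - a0)·k/(a0·a1)

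Worked case: a0 = 0.75, a1 = 0.85, s = 0.02, so k = 0.73 and g = 0.12; e = 4.5, h = 3.0. Without AI: (3.285 + 0.060)/0.75 = 4.460. With AI: (3.285 + 0.360)/0.85 = 4.288. Difference -0.172; the true value is 0.

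| Accuracy without → with AI | s | g | Difference, h = 3.0 | Difference, h = 3.5 |
|---|---|---|---|---|
| 75% → 80% | 2% | 7% | -0.091 | -0.061 |
| 75% → 85% | 2% | 12% | -0.172 | -0.115 |
| 80% → 90% | 2% | 12% | -0.163 | -0.108 |
| 85% → 90% | 2% | 7% | -0.081 | -0.054 |
| 70% → 85% | 3% | 18% | -0.253 | -0.169 |

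In this model the artefact is zero if accuracy does not change (a1 = a0) or if confidence is unrelated to which readings change (e = h). It turns positive if just one of the two signs is reversed, that is, if h exceeds e or if accuracy falls.

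**2. Simulation at the planned scale.** 40 readers by 500 images, with each reading's confidence score identical in both stages. Image difficulty was standard normal and reader skill normal with SD 0.4. Confidence was 3.7 - 0.7 × difficulty + 0.4 × skill plus noise of SD 0.6, rounded and held within 1 to 5. The log-odds of a correct reading were 1.6 - 1.2 × difficulty + skill, with 0.4, 0.8 or 1.2 added for AI. One data set was drawn per scenario.

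- Accuracy 0.79 → 0.84: correct-only difference -0.026 (paired t across readers -5.2)
- 0.79 → 0.88: -0.049 (t = -11.0)
- 0.79 → 0.91: -0.069 (t = -12.2)

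The differences are small on the scale, but with this many readings such an artefact could be reported as significant at 5%. The all-readings difference is 0 in every scenario.

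**3. Images correct in both stages.** In the worked case of step 1 this set is the 73% of readings with confidence e in both stages, so the difference is e - e = 0 and the artefact of step 1 disappears. The other 27% of reader-image pairs are left out, including the 12% that AI put right.

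**4. What leaves the comparison.** Readings per stage: 40 × 500 = 20,000. Wrong readings excluded: 5,000 at 75% accuracy, 4,000 at 80%, 3,000 at 85%, 2,000 at 90%.

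**5. Blindness to wrong readings.** Suppose confidence in correct readings is 4.2 in both stages, confidence in wrong readings rises from 3.0 to 4.0, and accuracy goes from 80% to 90%. The correct-only difference is 4.2 - 4.2 = 0. Over all readings the mean goes from 0.8 × 4.2 + 0.2 × 3.0 = 3.96 to 0.9 × 4.2 + 0.1 × 4.0 = 4.18, a change of +0.22.

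**The case against.** The article is condensed and the SAP is not shown. The analysis section does not say that no other confidence analysis will be done, and the Study design statement is unrestricted. A reader might infer that confidence in wrong readings will never be looked at; the article does not establish that. What stands is that the one confidence comparison whose image set is specified is narrower than the objective and design it serves. That is a stated choice, not a detail left open.

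A reader might also take it as settled that the two stages are compared on different images. The sentence does not say whether correctness is judged stage by stage or in both stages together. Under the second reading the case-mix artefact goes, as step 3 shows. Selection on outcome and the absence of wrong readings remain.

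The magnitudes are wholly assumed, and no single value from the table should be read as a prediction. Nor do the documents support calling this the loss of the study's main safety signal. The article does not label confidence a safety outcome. Wrong readings still count in sensitivity and specificity, and the management analysis covers children who would be discharged with a missed fracture. They leave one secondary comparison, not the study.

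Confidence in correct readings is a fair question in its own right, and the analysis of it can stay.

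**Conclusion.** The point holds as a mismatch between the stated analysis set and the confidence objective. Followed as written, the comparison is selected on an outcome AI may change and says nothing about confidence in wrong readings. The exclusion of wrong readings follows from the wording and needs no assumption. The case-mix artefact needs the stage-by-stage reading of correctness and a link between confidence and which readings change. Under the assumptions shown it runs from about -0.03 to -0.25 points, and both size and direction would move with other assumptions. One secondary objective is affected. The primary objective, the sample size and the data collection are not. The text should be corrected, and that can be done before analysis.

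**What to change.** Make the main confidence analysis the comparison of all readings with and without AI, paired by reader and case, using a model that allows for clustering by reader and by case. An ordinal mixed model with both as random effects is one option. This unconditional comparison is what removes the selection.

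Then report confidence for correct and for incorrect readings separately in each stage, as descriptive results, and keep the correct-only comparison as one of them. State there how correctness defines the set (stage by stage, or both stages) and that these subsets are selected on a post-AI outcome. An AI-by-correctness interaction, or a separate estimate for readings that are wrong with AI, conditions on the same outcome, so it does not remove the selection and should not replace the all-readings analysis. The descriptive split is still needed, because the overall mean does not show by itself where confidence rose.

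The cost is a change of analysis wording and a little more analysis work. The scores are already to be collected for every radiograph.

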**Methods and analysis:**

Using a multicentric dataset of 500 paediatric radiographs across four body parts, the diagnostic performance of HCPs will be evaluated across two stages—first without, followed by with the assistance of an AI tool (BoneView, Gleamer) after an interval 4-week washout period. The dataset will contain a mixture of normal and abnormal cases. HCPs will be recruited across radiology, orthopaedics and emergency medicine. We will aim for 40 readers, with ~14 in each subspecialty, half being experienced consultants. For each radiograph HCPs will evaluate presence of a fracture, their confidence level and a suitable simulated management plan. Diagnostic accuracy will be judged against a consensus interpretation by an expert panel of two paediatric radiologists (ground truth). Multilevel logistic modelling techniques will analyse and report diagnostic accuracy outcome measures for fracture detection. Descriptive statistics will evaluate changes in simulated patient management.

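### The objective asks whether AI alters management plans, but the analysis is limited to frequencies and percentages, so the change would carry no measure of uncertainty

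*Protocol article*

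**What the plan says.** Under Objectives, the protocol article gives the overall aim as finding out whether the AI tool "could help HCPs make better decisions about patient care". The third secondary objective is to "Determine whether management plans are altered following the use of the AI tool".

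Under Statistical methods/data analysis plan, the method for that objective is: "Changes in clinical management will be compared using descriptive statistics (ie, frequency and percentages"). One example given is "how many children would be discharged with a missed fracture"; the same sentence also names unnecessary second opinions or extra imaging. The abstract repeats the choice: "Descriptive statistics will evaluate changes in simulated patient management".

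The 95% CIs and p values in the same section are tied to the multilevel logistic models for the accuracy statistics, which are fitted "with the reader included as a random-intercept". Nothing similar is stated for management.

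Under Study design, "each reader (a HCP) will act as their own control across two imaging interpretation stages", and all readers read the same 500 cases at both stages. The management menu has seven options and differs by specialty.

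**The concern.** An objective worded as whether something is altered needs an estimate of the change and a statement of how far chance could explain it. A table of percentages for each stage supplies the first and not the second. The restriction is a stated method, introduced by an ie and repeated in the abstract. It is therefore not a detail that the article simply left for a fuller analysis plan.

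The design makes the missing interval hard for anyone else to supply. The decisions are paired (same reader, same case, two stages), and readers are fully crossed with cases. The quoted example counts children, yet each child with a fracture receives about 40 decisions per stage, so the number being counted is reader decisions. A published percentage based on thousands of decisions can look more precise than 181 children and 40 readers justify. The article also mentions that these figures could inform later estimates of benefit and savings, and such estimates would need a range.

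**Working it through.** **Inputs from the protocol article.** At least 40 readers; 500 cases; 181 children with a fracture; two stages; the same readers and cases in both. The article gives no sample size, expected rate or variance for management, so it has no figure of its own to reproduce on this point.

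**Counts per stage.**
- All management decisions: 40 × 500 = 20,000.
- On children with a fracture: 40 × 181 = 7,240.
- On the other 500 − 181 = 319 children: 40 × 319 = 12,760.

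**Standard error if decisions are treated as independent.** With n = 7,240 per stage and discharge rates p0 (without AI) and p1 (with AI), SE = √[(p0(1 − p0) + p1(1 − p1)) / n].
- 10% against 7% (assumed): √[(0.0900 + 0.0651) / 7,240] = 0.0046; 95% half-width 1.96 × 0.0046 = 0.9 points.
- 20% against 15% (assumed): √[(0.1600 + 0.1275) / 7,240] = 0.0063; half-width 1.96 × 0.0063 = 1.2 points.

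**Standard error that respects the design.** This comes from 1,500 simulated studies per setting, using a logistic model with reader, case, reader-by-AI and case-by-AI effects. The four standard deviations on the logit scale are assumptions. Ratios are from unrounded values.

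| Rates | SDs: reader, case, reader-by-AI, case-by-AI | SE | Ratio to independent SE | 95% half-width (points) |
|---|---|---|---|---|
| 10% v 7% | 0.5, 1.0, 0.2, 0.3 | 0.0057 | 1.22 | 1.1 |
| 10% v 7% | 0.5, 1.5, 0.3, 0.6 | 0.0066 | 1.42 | 1.3 |
| 10% v 7% | 0.7, 2.0, 0.5, 1.0 | 0.0083 | 1.79 | 1.6 |
| 20% v 15% | 0.5, 1.0, 0.2, 0.3 | 0.0079 | 1.26 | 1.6 |
| 20% v 15% | 0.5, 1.5, 0.3, 0.6 | 0.0098 | 1.56 | 1.9 |
| 20% v 15% | 0.7, 2.0, 0.5, 1.0 | 0.0121 | 1.93 | 2.4 |

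The ratio depends mainly on how much the effect of AI is allowed to vary between readers and between cases. Stable differences between readers or cases largely cancel in a paired difference. With the two AI-variation terms set to zero, the ratio falls to about 1. The trial can estimate this variation from its own reader-by-case data, but it cannot be read off marginal percentages.

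**The case against.** The strongest reply is that a declared descriptive analysis is not an error. Management is the third secondary objective and is simulated. The article is open about the method in both places, promises no significance claim for it, and lists the simulated choices among the study's limitations. All of that stands and limits the weight of the point. It does not remove the mismatch with an objective that asks whether plans are altered.

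A reader might infer several stronger things that the article does not support:
- **That decisions will be pooled over all readers.** The article does not say how percentages are aggregated. Because options differ by specialty, tables by specialty are at least as natural. The point does not need pooling, since percentages by reader or specialty would also lack an interval.
- **That management alone is denied a model or test.** Only the accuracy statistics have a named model and interval. For confidence scores the article says it will assess differences, and names no method.
- **That the figures are destined for an economic evaluation.** The article says only that they could help at a later implementation stage, where appropriate.
- **That the plan would publish intervals that are too narrow.** It proposes no interval for management. The ratios above describe what a later user would get from the counts.

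Nor need the wider interval change a conclusion. In another assumed setting the rate falls by 2.0 points, with a standard error of 0.74 points, against 0.48 under independence. The half-widths are 1.96 × 0.74 = 1.45 and 1.96 × 0.48 = 0.94, so −3.45 to −0.55 and −2.94 to −1.06 both exclude zero.

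Finally, an unseen analysis plan might add intervals. That is possible, but it would go beyond a method that the article states explicitly and twice.

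**Conclusion.** The point holds in a modest form. The method stated for the third secondary objective cannot answer the question that the objective asks, because it gives a change with no measure of uncertainty. This follows from the text alone and rests on no assumption. No number in the article is wrong, and the primary objective is unaffected.

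The size is illustrative. On the assumed rates and variance components, a standard error that respects readers and cases is about 1.2 to 1.9 times the independent one. For 10% against 7%, the half-width is 1.1 to 1.6 points rather than 0.9; for 20% against 15%, it is 1.6 to 2.4 rather than 1.2. If the AI effect hardly varied between readers or cases, the gap would be small. This is a cheap improvement, not a fault that endangers the trial.

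**What to change.** Keep the descriptive tables and present them by specialty, since the options differ. For the binary outcomes the analysis section already names (discharge when a fracture is present; second opinion or additional imaging when none is present), add the paired difference, with AI minus without AI, and a 95% CI that accounts for both readers and cases. Either of these would do:
- a bootstrap that resamples readers and cases, keeping each reader's two stages together; or
- a logistic model with crossed reader and case effects, letting the AI effect vary between readers and between cases, with the result expressed as a difference in percentages.

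A reader random intercept alone, as planned for the accuracy models, would not cover variation between cases. Give denominators as reader decisions, with the numbers of readers and children beside them.

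The cost is a few lines of text and code, with no new data. The downside is that the management result may turn out inconclusive.
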